### Quantitative phase

#### Design.

A two-arm cluster randomised controlled trial will be conducted following the recommendations of the CONSORT checklist [46]. A six-week online intervention will be carried out using exercise videos, taking into account the current scientific evidence and the results of the previous phase. The intervention will align with established guidelines [47], which emphasises therapeutic exercise, including strengthening exercises, mobility and stretching routines, and general physical activity, to improve musculoskeletal function and address musculoskeletal disorders.

In this study aimed at reducing musculoskeletal spinal pain among university office workers, two distinct interventions are being employed: the Intervention Group and the Control Group.

The Intervention Group will implement a six-week therapeutic exercise intervention in their workplace environment, following the program content developed in the previous phase.

Conversely, participants in the Control Group will be placed on a waiting list, advised to maintain their regular daily activities, and working hours. Upon completion of the questionnaires after the six weeks, they will gain access to the platform, receiving identical content to that of the Intervention Group.

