#### Sample size calculation.

The GRANMO calculator has been used to obtain the sample size. The study by Kenneth et al [48], has been taken for reference with a minimum significant difference in pain intensity of 1.5 and a standard deviation of 1.5, considering an alpha risk of 0.05 and a statistical power of 95% to reject the null hypothesis, the minimum number of participants per group necessary will be 33 accounting for an expected 20% dropout rate.

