#### Randomisation: type and sequence generation.

Participants in the study will be assigned to either the Intervention Group or the Control Group through cluster randomisation. The six campuses of the University will be randomised into either group to prevent contamination between groups. A 1:1 ratio will be maintained to ensure an equal distribution of campuses between the experimental and control clusters. The randomisation will be conducted using Study Randomizer, a web-based service, to ensure unbiased allocation [49].

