#### Statistical analysis.

Descriptive statistics will be used to summarise the demographic and baseline characteristics of participants. Categorical variables (e.g., gender, educational level) will be compared between control and intervention group using Chi-square tests or Fisher’s exact tests, as appropriate, while continuous variables (e.g., age) will be compared using independent-samples t-tests for normally distributed variables or Mann–Whitney U tests if the data are not normally distributed. The Shapiro-Wilk test and Q-Q plots will be employed to assess normality. If the data meet normality assumptions (p > 0.05), parametric tests will be applied; otherwise, non-parametric tests will be used.

Within-group comparisons (before- vs. after-intervention) will be conducted using paired t-tests for normally distributed variables, and the Wilcoxon signed-rank test will be applied for variables not meeting normality assumptions. Changes from baseline between the intervention and control groups (before and after differences) will be evaluated using independent-samples t-tests for normally distributed data, or Mann–Whitney U tests for non-normal data. Clinically significant changes will be assessed using criteria established in previously reviewed studies.

Mixed-effects models will be employed to evaluate the effect of the intervention over time, taking into account repeated measures. A linear mixed-effects model will be applied to outcomes that are approximately normally distributed, with random intercepts included to account for within-subject variability. If an outcome clearly violates normality assumptions even after exploration or transformation, a generalized linear mixed model (GLMM) with an appropriate link function (e.g., logit for binary outcomes) may be considered. These models will adjust for potential confounders such as age, gender, educational level, spinal pathologies, job tasks, and adherence. Statistical significance will be set at a p-value of less than 0.05. Mixed-effects models are appropriate for this cluster-randomised design with repeated measures, as they account for both fixed effects and within-subject variability. Sample size was estimated assuming a moderate effect size, an ICC of 0.05, alpha = 0.05, and 80% power.

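### Campuses are randomised, but no between-group analysis described in the protocol accounts for campus, and the reason given for the mixed model concerns the wrong level

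*Protocol article*

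**What the plan says.** The Design section of the quantitative phase calls the study a cluster trial: "A two-arm cluster randomised controlled trial will be conducted following the recommendations of the CONSORT checklist". The randomisation section names the unit, "The six campuses of the University will be randomised into either group to prevent contamination between groups", and fixes the ratio, "A 1:1 ratio will be maintained to ensure an equal distribution of campuses between the experimental and control clusters". That gives three campuses per arm.

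Statistical analysis then describes two kinds of between-group analysis:

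- Change from baseline is compared between arms by an independent-samples t-test, or by a Mann-Whitney U test if the data are not normal.
- A linear mixed model (or a generalised one for non-normal outcomes) is fitted "with random intercepts included to account for within-subject variability". The adjustment variables it names are personal and job characteristics, spinal pathology and adherence. Campus is not among them.

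The model is defended in these words: "Mixed-effects models are appropriate for this cluster-randomised design with repeated measures, as they account for both fixed effects and within-subject variability". The next sentence of that section reports an ICC of 0.05 as a sample-size assumption. No outcome is attached to it, and it is not carried into any analysis.

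**The concern.** When campuses are allocated, anything that shifts a whole campus (workload, management, a local event during the six weeks) falls entirely on one arm. With three campuses per arm such shifts do not average out, and an analysis at worker level counts them as treatment effect. A random intercept for the worker handles the correlation between the two measurements on one person. It does not handle the correlation between different workers on the same campus.

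At stake is the error rate of the main effectiveness comparison. By quoting an ICC the authors show that they expect some campus correlation, but the described tests and model make no allowance for it. The article also asserts that the model is suited to the design, so a reader would take the resulting p-values and intervals as cluster-adjusted when they are not.

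**Working it through.** **Inputs from the protocol.** Six campuses at 1:1 (Randomisation). From Sample size calculation: a VAS difference of 1.5 with SD 1.5, a 5% level, 95% power, and 33 workers per arm after allowing for 20% dropout. ICC 0.05 (Statistical analysis, last sentence).

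**Step 1. Reproduce the stated size.** For two independent means, n per arm = 2 × (1.960 + 1.645)² × (1.5/1.5)² = 25.99, so 26. Dividing by 0.8 for dropout gives 32.5, so 33. The stated figure reproduces with a two-sided 5% level and a design effect of 1. About 26 per arm (52 in all) would be analysed after dropout, and 33 per arm (66) with none.

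**Step 2. Design effect.** Assume that ICC 0.05 applies to the analysed outcome and that campuses are of equal size. DE = 1 + (m − 1) × ICC.

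| | 26 per arm | 33 per arm |
|---|---|---|
| Workers per campus, m | 26/3 = 8.67 | 33/3 = 11 |
| DE | 1 + 7.67 × 0.05 = 1.38 | 1 + 10 × 0.05 = 1.50 |
| True SE / naive SE = √DE | 1.18 | 1.22 |
| Naive SE too small by 1 − 1/√DE | 15% | 18% |
| Type I error, 2 × (1 − Φ(1.96/√DE)) | 9.6% | 11.0% |

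**Step 3. Simulation of the worker-level t-test under the null** (three against three campuses, 100,000 runs per scenario).

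- ICC 0.05: 9.6% with campuses of 9, 9 and 8; about 11% with campuses of 11; about 11% with unequal campuses of 4, 8 and 15.
- Other assumed ICCs, campuses of 9, 9 and 8: about 6% at 0.01, 7% at 0.02 and 14% at 0.10.
- A t-test on campus means with 4 degrees of freedom stays at about 5% or slightly below.

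**Step 4. Change scores.** The described t-test is on change, and a campus effect that is constant over time cancels from change. Assume that campus accounts for 0.05 of the variance at each visit, that the within-person correlation of the remaining 0.95 is 0.5, and that a fraction s of the campus variance is stable.

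- Campus variance of change = 2 × 0.05 × (1 − s).
- Worker variance of change = 2 × 0.95 × (1 − 0.5) = 0.95.
- ICC of change = 0.10(1 − s) / [0.10(1 − s) + 0.95].

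| Stable fraction s | ICC of change | Simulated type I error, campuses of 9 |
|---|---|---|
| 1 | 0 | about 5% |
| 0.8 | 0.02/0.97 = 0.021 | about 7% |
| 0.5 | 0.05/1.00 = 0.05 | about 10% |
| 0 | 0.10/1.05 = 0.095 | about 15% |

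**Step 5. Interval width with 52 analysed, SD 1.5, ICC 0.05.** The naive half-width is 2.009 × 1.5 × √(2/26) = 0.84 VAS points. At campus level on 4 degrees of freedom it is 2.776 × 1.5 × √(2 × 1.383/26) = 1.36 points.

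**The case against.** Three points can fairly be made for the plan.

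First, the wording is not closed. Random intercepts are in the plural, the list of adjustment variables is introduced as examples, and the sentence defending the model mentions the cluster design. A campus term is not ruled out, so a reader who inferred that campus has been deliberately excluded would go too far. What stands is narrower: no campus term is named, the only stated purpose of the intercepts is within-subject variability, and the t-test and Mann-Whitney test as described have no place for one.

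Second, a reader might infer that the intervals must be too narrow and the 5% level must be broken. The documents do not establish that. The ICC belongs to no stated outcome, and Step 4 shows that campus effects fully stable over six weeks would leave a change-score test at its nominal level. This limits the size of the problem but does not remove it. The protocol offers no argument that campus effects are stable, and a valid analysis should not depend on that.

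Third, such detail could be left to a separate analysis plan. That would answer silence. Here the article states the tests and the random-effect structure and claims that they suit the design for a reason that does not bear on clustering by campus.

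**Conclusion.** The point holds as a fault in a stated analysis. Six campuses are randomised, and no between-group analysis described takes account of campus. Handling within-subject variability does not make the mixed model suited to a cluster design. That part rests on the text alone and is firm.

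The size is conditional. If ICC 0.05 applies to the analysed outcome, the nominal 5% test has a true type I error of about 10 to 11%. For change scores the range is about 5 to 15%, given an assumed within-person correlation of 0.5 and a campus share of 0.05. The protocol gives no basis for choosing a value within that range. Because the fault touches the main effectiveness inference and is cheap to repair, it should be corrected before outcomes are analysed.

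**What to change.** Make the primary between-group comparison one that respects campus, with about 4 degrees of freedom (six campuses less two arms). Either of these would do:

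- a two-stage analysis: a t-test on the six campus means of change in VAS or of baseline-adjusted VAS; or
- a linear mixed model of follow-up VAS, adjusted for baseline VAS, with a random intercept for campus and a small-sample correction such as Kenward-Roger.

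If the pre/post repeated-measures model is kept, it needs a campus-by-time random effect with the same small-sample care. A campus intercept alone absorbs only the time-constant part and does not protect the arm-by-time contrast. In a small simulation (400 runs) with half the campus variance stable, a model with campus and subject intercepts still rejected 11.8% of the time.

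Keep the participant-level t-test and Mann-Whitney test as descriptive only, or drop them. Replace the sentence that justifies the model by within-subject variability with one that says how campus is handled.

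The cost is revised analysis wording, a little more analysis work and wider intervals (half-width about 1.36 instead of 0.84 VAS points under the assumptions of Step 5). No new data or change of design is needed.

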An intention-to-treat analysis will be conducted, ensuring that all participants are analysed in their originally assigned groups. Missing data will be addressed using complete-case analysis, assuming data are missing at random. Sensitivity analyses will be considered to assess the potential impact of missingness on the results. All statistical analyses will be performed using STATA v.16 software [50].

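### Complete-case analysis contradicts the promise to analyse all participants, and missing at random does not in general justify it for the unadjusted change-score tests

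*Protocol article*

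**What the plan says.** The last paragraph of Statistical analysis makes three statements in sequence. The first concerns the analysis population: "An intention-to-treat analysis will be conducted, ensuring that all participants are analysed in their originally assigned groups". The second concerns missing values: "Missing data will be addressed using complete-case analysis, assuming data are missing at random". The third is "Sensitivity analyses will be considered to assess the potential impact of missingness on the results", which names no method.

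Three other places determine what this means in practice:

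- Sample size calculation sets "the minimum number of participants per group necessary will be 33 accounting for an expected 20% dropout rate".
- Data collection and analysis (quantitative phase) schedules questionnaires at baseline and at six weeks only.
- Statistical analysis compares the arms by independent-samples t-tests or Mann–Whitney tests on change from baseline, without covariates. It also plans mixed-effects models with random intercepts. It does not say which of these is the main comparison, or whether the models keep participants who have only a baseline value.

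**The concern.** There are two separate problems.

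The first is the analysis set. A participant without a six-week questionnaire has no change score, so a complete-case rule removes that person. The remaining set is completers analysed in their assigned arms, not all participants.

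The second is the justification. Missing at random allows dropout to depend on observed data such as arm and baseline pain. An unadjusted comparison of change scores among completers is not protected against that. It needs missing completely at random, or a special case such as the same dependence on baseline in both arms. Missing at random does support a likelihood-based model fitted to all available data. If the complete-case rule is also applied to the mixed model, that benefit is lost.

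Different dropout mechanisms by arm are plausible here. The intervention arm is asked to keep a daily diary and receives weekly prompts, while waiting-list controls gain platform access once they have completed the six-week questionnaires. At stake are a modest bias in the pain comparison and a result that would be labelled intention-to-treat when it is not.

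**Working it through.** **Step 1: reproduce the planned number.** Inputs from Sample size calculation: "a minimum significant difference in pain intensity of 1.5 and a standard deviation of 1.5" and "considering an alpha risk of 0.05 and a statistical power of 95% to reject the null hypothesis". Taking the test as two-sided:

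n per arm = 2 × (1.960 + 1.645)² × (1.5/1.5)² = 25.99, rounded up to 26. Allowing for 20% dropout: 26/0.8 = 32.5, rounded up to 33. The stated figure is reproduced.

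The later statement in Statistical analysis, "Sample size was estimated assuming a moderate effect size, an ICC of 0.05, alpha = 0.05, and 80% power", describes different assumptions. That is a separate matter and does not affect what follows.

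**Step 2: who is excluded.** 0.20 × 33 = 6.6 per arm, so about 6 to 7, or 13 of 66 in total. About 26 per arm remain. Power at 26 per arm is 95.0% under individual randomisation, so this loss is already allowed for in the numbers.

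**Step 3: size of the bias under missing at random.** Let z be standardised baseline pain, ρ the correlation between baseline and six weeks, σ the SD (equal at both times), and the true effect zero. The expected change given baseline is −(1 − ρ)σz. If dropout depends only on arm and baseline, then

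bias = −(1 − ρ) × σ × (mean z in intervention completers − mean z in control completers).

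The documents give neither ρ nor the dropout mechanism, so both are assumed.

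*Illustration.* Dropout probability Φ(−0.95 − 0.6z) in the intervention arm, none in controls, ρ = 0.5, σ = 1.5.

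- √(1 + 0.6²) = 1.166 and 0.95/1.166 = 0.815.
- Proportion retained = Φ(0.815) = 0.792, so dropout is 20.8%.
- Mean z in intervention completers = (0.6/1.166) × φ(0.815)/0.792 = 0.5145 × 0.286/0.792 = 0.186.
- Bias = −0.5 × 0.186 = −0.093 SD, and −0.093 × 1.5 = −0.14 VAS points.
- Relative to the target: 0.14/1.5 = 9%.

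A simulation of the same scenario gave −0.092 SD.

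*Range.* Simulation with 1,000,000 per arm, 20% dropout in each arm, logistic dependence on baseline (slope per SD), σ = 1.5 and no true effect. Entries are the bias of the complete-case change-score difference in VAS points.

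| Slope, control / intervention | ρ = 0.3 | ρ = 0.5 | ρ = 0.7 |
|---|---|---|---|
| 0 / 0 | about 0 | about 0 | about 0 |
| 1 / 1 | about 0 | about 0 | about 0 |
| 0 / 1 | 0.18 | 0.13 | 0.08 |
| 0 / −1 | −0.18 | −0.13 | −0.08 |
| −1 / 1 | 0.36 | 0.26 | 0.15 |

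Where bias arises, it runs from 0.08 to 0.36 points in absolute size: 0.08/1.5 = 5% to 0.36/1.5 = 24% of the target. It can go in either direction. A baseline-adjusted analysis of covariance on the same complete cases gave about 0 in every row.

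**Step 4: does the mixed model help?** With two time points and complete pairs only, the arm-by-time estimate of a random-intercept model equals the difference in mean change. In a simulation with 21% baseline-dependent dropout in the intervention arm only (20,000 per arm, ρ = 0.5), both were −0.116 points. The same model fitted to all available data gave +0.02, within simulation error of zero. Keeping the baseline-only participants is what removes the bias.

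**The case against.** The strongest reply is that complete-case analysis is not itself the culprit. Step 3 shows that adjusting the same complete cases for baseline removes the bias when dropout depends only on arm and baseline. That stands: the fault lies in pairing complete cases with an unadjusted change score, and the likelihood analysis is one remedy among several. A reader might infer that complete-case analysis always requires missing completely at random. It does not.

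The intention-to-treat sentence can also be read as meaning analysed as randomised, and the complete-case sentence does not expressly remove baseline-only participants from the mixed models. Both readings are possible. Even so, a claim to analyse all participants overstates a completer set, and the models' analysis set needs stating.

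Several stronger readings are not supported:

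- **Unequal dropout rates alone cause bias.** They do not. Dropout of 10% against 30% at random gives 0.00. Dropout must also depend on baseline pain, and the documents give no evidence on that. They do plan email and telephone follow-up of non-responders.
- **The trial loses power.** The 20% inflation already covers the loss (Step 2).
- **Adjusting for adherence would delete the control arm.** The protocol does not say that control adherence would be coded as missing.
- **Dropout through lack of benefit strengthens the case for this fix.** With no assessment between baseline and six weeks, that benefit is unobserved in dropouts. In a check of this case, the bias of −0.28 points fell only to −0.22 under a missing-at-random analysis.
- **The absence of a named not-at-random analysis is a defect.** That detail belongs in a statistical analysis plan, and the article does mention sensitivity analyses.

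**Conclusion.** The point holds in a limited form. The protocol claims an analysis of all participants but specifies one of completers, leaving out about 6 to 7 of 33 per arm at the expected dropout. Its stated assumption does not in general justify its stated method for the unadjusted change-score tests.

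The invalidity is conditional: the tests are not guaranteed valid, rather than always biased. The bias needs dropout that depends on baseline pain differently by arm. The illustrated 0.14 points rests on an assumed correlation of 0.5, an SD of 1.5 and an invented mechanism that puts all dropout in one arm. The upper end of the range requires opposite dependence in the two arms. These sizes are modest against 1.5 points, so the plan should be changed, but the trial is not undermined.

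**What to change.** - Make the between-arm comparison the mixed model already planned, fitted by maximum likelihood or REML to all randomised participants with at least one VAS value, with baseline VAS in the outcome vector. Multiple imputation by arm that respects campus is an alternative.
- State that this is the analysis valid under missing at random, and that participants with only a baseline value are kept.
- Keep complete-case analysis as a sensitivity analysis, described as completers analysed as randomised.
- If a complete-case comparison is retained, adjust it for baseline VAS. This removes the bias when dropout depends only on arm and baseline.

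The cost is analysis wording and a little programming. The sample size does not change and no extra data are needed.

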#### Ethical considerations.

This study will adhere to the principles outlined in the Declaration of Helsinki and the guidelines of Good Clinical Practice. The study protocol has obtained approval from the Research Ethics Committee (CEIm) of the Hospital Universitari Arnau de Vilanova under the reference CEIC-2842.

#### Validity and reliability/rigour.

The mixed methods study description was developed following the guidelines of the Good Reporting of a Mixed Methods Study (GRAMMS) statement [64], and the SPIRIT Checklist and Schedule (Fig 1) for reporting clinical trials [65].

**Fig 1 pone.0325376.g001:**
[figure not shown]
SPIRIT schedule of enrolment, interventions, and assessments. Schedule of enrolment, allocation, interventions, and data collection based on the SPIRIT 2013 guidelines for the present study.

## Discussion

The digitalisation of our society has accelerated exponentially due to the COVID-19 pandemic [66], driven by restrictions on movement, physical inactivity and sedentary lifestyles, which had already alarming levels before the pandemic occurred, and great efforts are needed to try to curb this situation [67]. An active lifestyle provides physical, cognitive and psychological benefits for people’s health [68,69]. Workers with long working hours and low physical activity levels in their tasks have lower daily activity levels than the average population [70], so taking advantage of breaks at work by taking active breaks can be an interesting option.

The possibilities offered by digitalisation, such as internet access and applications that remind workers via email or push notifications to take breaks, can facilitate the implementation of active breaks [71]. Research has shown that digital health interventions provide widely accessible, cost-effective, and scalable methods for managing musculoskeletal conditions, significantly reducing pain and improving functional disability [72]. In particular, tools such as audio-visual resources, emails or video calls allow patients to follow treatment plans remotely, providing flexibility and convenience [73]. While these interventions can be a significant step forward by helping patients take control of their recovery, self-manage their conditions, and maintain adherence to treatment, the broader applicability of these digital self-management tools remains uncertain, especially given the limited evidence on cost-effectiveness and patient diversity [74].

Studies have highlighted the importance of multi-component interventions that consider individual and contextual factors in reducing sitting time for long-term behavioural change [75,76]. In addition, influencing motivational aspects of sitting time reduction, both automatic and reflective motivation, is key to engaging workers in this type of intervention [77]. Considering these insights, the proposed workplace exercise intervention tends to incorporate automatic motivation through reminders and reflective motivation through educational components to help workers understand the importance of reducing musculoskeletal pain. This approach is supported by research suggesting that both types of motivation can significantly enhance engagement and adherence to interventions, particularly those focused on increasing physical activity [78]. This dual approach aligns with SDT [28], which posits that autonomous motivation (e.g., internalised health goals) enhances long-term engagement, while controlled motivation (e.g., external prompts) facilitates initial behaviour change.

This framework is supported by digital health research, highlighting the effectiveness of combining intrinsic and extrinsic motivational strategies. Peters et al [79], emphasise that digital health interventions designed with SDT principles, including autonomy-supportive elements, personalised feedback, and gamification, improve engagement and adherence. Similarly, other studies have found that integrating reflective processes (e.g., self-monitoring and goal-setting) with automatic cues (e.g., digital nudges and notifications) significantly enhances sustained behaviour change [80,81].

There are no clear guidelines on the optimal dose of physical activity for chronic pain treatment, but reducing sedentary time and increasing movement are known to be beneficial [82]. There is uncertainty about which exercise interventions in treating chronic pain might be the best option, but what has been observed is that a biopsychosocial approach is effective [83]. However, despite being low-cost interventions that are feasible to implement in the workplace, some factors can act as barriers, such as workload or organisational aspects [84]. A preliminary phase using semi-structured interviews to determine the expectations and beliefs of office workers will help us ensure that the subsequent intervention with physical exercise is adapted to the needs of this group and the context in which they find themselves during their working day.

Adopting a sequential exploratory mixed-methods approach allows for a more comprehensive understanding of workplace interventions by integrating qualitative insights with quantitative evaluation. Unlike the workplace interventions included in the current systematic review on this topic [17], which primarily implement predefined exercise programs without detailing how they were selected or tailored to workers’ needs, this study actively integrates workers’ experiences through a qualitative phase [85]. This ensures that the intervention aligns with their real-world constraints and expectations, enhancing feasibility and adherence. Mixed-methods studies are gaining relevance in the field of public health [86], with some studies suggesting that a multidimensional approach needs to be considered in the current framework to achieve relevant results [86,87]. There are other mixed methods protocols in musculoskeletal pathology in chronic low back pain [88] and women with fibromyalgia [89] that focus on this approach in which a qualitative intervention is carried out to understand the expectations and context of the patients, before designing the quantitative intervention subsequently.

